### 2.2. Participants and Settings

The study will be conducted in a research center in Galicia; a non-profit organization under private law whose aim is to contribute to the strengthening, empowerment, growth, and improvement of the competitiveness of the Galician information and communication technologies (ICT) sector. Sample selection will be performed through intentional sampling based on inclusion and exclusion criteria.

The participant inclusion criteria is: (a) performing management/administration/research tasks at the research center.

The participant exclusion criteria is: (a) close to retirement (5 years or less); (b) significant health condition complications that prevented active participation in the study; and (c) hypersensitivity in the skin or a recognized allergy to the material of the cases or straps of the wearable wristbands used as one of the measuring instruments of the study.

### 2.3. Recruitment Process

Entry into the study field will occur at the workplace where the project will be held. The participants will be recruited at the workplace, through an informative meeting that will be conducted at the facilities. In this meeting, the selection criteria for the study and the implications of participating will be presented, highlighting the total duration of participation and the mechanisms that will be followed at an ethical level to guarantee anonymity and the confidentiality of the data.

After the presentation of the main characteristics of the study to the workers attending the meeting, the information sheet will be given to any interested person to consider for as long as they wish, before making a decision regarding participation.

A week later, those workers willing to participate will be visited again to carry out the process of informed consent with the Principal Investigator (PI). In these individual meetings, possible doubts or queries will be resolved, the established selection criteria will be checked for each person, and the informed consent document will be signed if applicable.

### 2.4. Justification of Sample Size

This pilot study is being suggested in order to determine the feasibility, time, and cost required for a subsequent study, as well as to demonstrate that the selected measurements and instruments are feasible and effective, and to determine, based on the results, the optimal frequency, intensity, and duration of the study.

Likewise, by carrying out this pilot study, we will gain information about the standard deviation and the proportion of participants with the specific characteristics needed for this study, which will allow us to carry out the calculation of the sample size.

### 2.5. Outcomes

The primary outcome will be to determine the influence of stress and anxiety on the worker. The secondary measures will be: (a) sleep recording and physical activity tracking with the Xiaomi Mi Band 3; (b) quality of life self-perception with the EuroQol 5D-5L (EQ 5D-5L) scale; (c) determination of sleep habits by using the Pittsburgh Sleep Quality Index (PSQI); (d) anxiety self-perception by using the State-Trait Anxiety Inventory (STAI); (e) stress self-perception by using the Perceived Stress Scale-10 (PSS-10); and (f) influence of stress on daily functioning, by using a questionnaire designed by a work stress psychologist professional in consensus with the socio-sanitary professionals of the group.

### 2.6. Data Collection and Management

Prior to any other data, socio-demographic features of the participants considered as relevant will be collected using a record sheet of our own elaboration. This questionnaire includes questions regarding age, gender, marital status, residential environment, cohabitation unit, educational level, profession, socio-economic level, working hours, overtime working hours, level of perceived stress, other non-work-related stress factors, actions oriented to stress reduction, and medication intake.

Data will be collected from different sources (Figure 1). For biometrical data, a Xiaomi Mi Band 3 will be worn by all the participants for six months to measure their physical activity (steps), sleep (hours of sleep and sleep stages), and heart rate (bpm). A self-developed data collection system will be installed in one of the computers of the research center, capturing the data from the wristbands via Bluetooth every time they walk nearby and storing it in an Structured Query Language (SQL) database [59]. When the data is analyzed, it will be retrieved by the SQL database in which it was stored. The data will be exported through CSV in a detailed or accumulated way for analysis in any statistical program.

The Research Electronic Data Capture Consortium (REDCap), a safe web application to create and manage online surveys and databases [60], will be used to digitally create the questionnaires and tests explained below, which will be sent to the participants to fill out.

In this study, participants will complete a set of assessment tools and a self-made questionnaire associated with work overload, sleep, and physical activity. These assessment tools will be filled in at the beginning and end of the study, while the self-made questionnaire will be answered throughout the study. This information is shown in Table 1.

The scales to be completed are: (1) the EQ 5D-5L, which evaluates mobility, personal care, daily activities, pain/discomfort, anxiety/depression, and global status at the moment of assessment [61], (2) the PSQI, which analyzes the quantity, quality, duration, latency, and efficiency of sleep [62], (3) the STAI, which evaluates the presence of anxiety [63], and (4) the PSS-10, which measures the degree to which, during the last month, people have felt annoyed or worried or, on the contrary, have felt confident in their ability to control their personal problems [64].

Finally, a self-made questionnaire was developed considering the results of a prior poll that assessed different factors potentially related to stress. Those items that were directly related to stress were chosen for the questionnaire. This final questionnaire was agreed on by a stress psychologist professional. It is composed of three daily and four weekly items to answer (Appendix A), related to stress, work commitment and frustration, sleep, physical activity, and occupational balance. All items in the weekly and daily questionnaire are scored from 0 to 5 (0 = Nothing; 1 = Very little; 2 = Little; 3 = Some; 4 = Quite a lot; 5 = A lot).

### 2.7. Data Analysis

The statistical treatment of the data will be performed with the statistical package IBM SPSS Statistic version 22 (IBM, Chicago, IL, USA). The significance level for hypothesis testing is set at 5%. The numerical variables will be expressed as the mean (M) and standard deviation (SD), including range, minimums, and maximums, while the categorical variables will be shown with their absolute frequency and valid percentage. In addition to the simple description of the data and variables studied, inferential analyses will be conducted in order to determine possible significant relationships between the variables of the study, or to allow the contrast of hypotheses. The Kolmogorov–Smirnov test will be applied to check that the variables behave as a normal distribution [65]. If not, non-parametric tests will be used in the subsequent analysis. The association of numerical variables will be analyzed with the Pearson or Spearman’s Rho correlation test, depending on the distribution of the sample. To assess the association of categorical variables, the Chi-square test will be applied, or the likelihood ratio in the case that the frequencies observed are less than 5%. In the case of the association between quantitative and qualitative variables, the comparison of means will be made with Student’s *t*-test and analysis of variance (ANOVA) or Mann–Whitney and Kruskal–Wallis’ U test, as appropriate [66]. Finally, and in order to determine whether there are significant and relevant differences between the results of the evaluations performed (initial, intermediate, and final), the Wilcoxon test will be applied [66]. Data analysis includes the cleaning or pre-processing, description, and processing of the stored data. The final objective of these steps is to obtain information for decision making. During pre-processing, erroneous data are removed or corrected to avoid bias in the results. Subsequently, a descriptive statistical study which summarizes certain relationships and distributions in a simple way will allow us to choose which processing strategy to adopt.

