### Objectives

The main objective of this study is to assess the work stress level and its influence on the quality of life of workers at a research center.

The specific objectives are:—To itemise the level of some parameters, such as activity, sleep, and heart rate.—To determine the level and impact of occupational stress in worker’s daily life through the information from wristbands and questionnaires.—To identify patterns of occupational functioning, physical activity, and sleep in these people.—To study the association between the identified patterns of occupational functioning, activity, and sleep, and the level of occupational stress and quality of life.

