## 2. Materials and Methods

### 2.1. Study Design

This project will be a pilot study to determine the viability, sample size, cost, and duration of the study. Additionally, this project has been designed in order to “demonstrate that the planned measurements, the data collection instruments, and the data management system are feasible and effective” [57]. If this study proves to be successful, it will be performed with a larger sample from different work settings.

This study will be observational, analytical, and longitudinal. That is, in this study, different variables of the population under study will be observed and recorded without intervention, and with the aim of establishing causal associations between variables. It is considered longitudinal because the variables will be followed for six months, with continuous recording and monitoring of physical activity and the quality of sleep (wristbands). Variables related to work stress, quality of life, and perception of the quality of sleep and the level of physical activity (specific evaluation tools) will also be specifically measured [57]. This study protocol will follow the SPIRIT 2013 guidelines (See File S1) [58].

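### Section 2.7 assigns every association to tests that need one independent observation per worker, but the stress items and wristband data are repeated and the unit of analysis is not fixed

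*Protocol article*

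**What the plan says.** **Tests.** Section 2.7 sets a 5% significance level and gives one rule for each type of variable pair:
- Numerical pairs: "The association of numerical variables will be analyzed with the Pearson or" Spearman coefficient, depending on distribution.
- Categorical pairs: "To assess the association of categorical variables, the Chi-square test will be applied", or the likelihood ratio when frequencies are low.
- Mixed pairs: "In the case of the association between quantitative and qualitative variables, the comparison of means will be made with" the t-test and ANOVA, or their rank-based counterparts.

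The only method for repeated measurements concerns change between assessment rounds: "differences between the results of the evaluations performed (initial, intermediate, and final), the Wilcoxon test will be applied". No method for association between repeated records is named.

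**Data.** Section 2.1 describes the design: "It is considered longitudinal because the variables will be followed for six months". The Introduction says the wristband gives values minute by minute. Section 2.6 and Table 1 add three daily and four weekly items, each scored 0 to 5, while the standard scales are completed only two or three times. On the wristband data, section 2.6 says: "The data will be exported through CSV in a detailed or accumulated way for analysis in any statistical program".

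**Purpose.** The fourth specific objective begins "To study the association between the identified patterns of occupational functioning, activity, and sleep" and relates these patterns to the level of occupational stress and quality of life.

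**The concern.** The listed tests take their standard error from the number of rows, as if each row came from a different person. The variables that matter most for the fourth objective have many rows per person. The article does not say whether a row in the analysis is a worker, a week, a day or a minute, and the choice matters.

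- **Rows pooled.** Stable differences between workers count as many independent pieces of evidence. Two unrelated variables that each differ between workers will then look associated too often.
- **One value per worker.** The tests are valid but can only say whether workers with higher average stress also sleep or move differently. Whether a worker's own bad weeks go with worse sleep or less activity is left unexamined, although the data to examine it are collected.

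The results are meant to feed a larger study, and section 2.1 states an aim of establishing causal associations. Spurious findings, or unused within-worker information, would carry forward.

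**Working it through.** The article gives no sample size, power or effect size, so there is no figure of its own to reproduce.

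**Inputs from the article.** Significance level 5% (taken as two-sided); follow-up six months; daily and weekly items.

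**Assumptions.** Six months is about 26 weeks, so m = 26 weekly records, or 26 × 5 = 130 working-day records. The ICC is the share of a variable's variance that lies between workers. It is taken as equal in both variables and varied from 0.05 to 0.5. Correlation within a worker is exchangeable.

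**1. Pooled rows, Pearson test, no true association.**

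Variance inflation: D = 1 + (m − 1) × ICC²

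True type I error: 2 × (1 − Φ(1.96/√D))

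| ICC | D, m = 26 | Error | D, m = 130 | Error |
|---|---|---|---|---|
| 0.05 | 1.06 | 5.7% | 1.32 | 8.8% |
| 0.1 | 1.25 | 8.0% | 2.29 | 19.5% |
| 0.2 | 2.00 | 16.6% | 6.16 | 43% |
| 0.3 | 3.25 | 28% | 12.61 | 58% |
| 0.5 | 7.25 | 47% | 33.25 | 73% |

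Example: m = 26, ICC 0.5 gives D = 1 + 25 × 0.25 = 7.25; 1.96/√7.25 = 0.728; error = 0.467.

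Simulation with 20 and 40 workers (1,000 runs per cell) agreed. At ICC 0.3 and 0.5 it gave 28-31% and 46-48% for 26 records, and 56-59% and 71-73% for 130. The number of workers hardly mattered. With only three scale rounds pooled, D at ICC 0.5 is 1 + 2 × 0.25 = 1.5 and the error 11%; at ICC 0.05 it is 5%.

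**2. One value per worker.** In the same simulations, Pearson on worker means rejected in 3.5-6.3% of runs, which is consistent with 5%. What is lost shows in a second simulation: true within-worker correlation 0.3, none between workers, ICC 0.5. Worker means rejected in 4-6% of runs. A test on deviations from each worker's mean rejected in 100%. That simulation had no serial correlation, so 100% is a best case.

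**3. Does a random intercept suffice as a remedy?** Suppose the average within-worker slope is zero but individual slopes vary with SD 0.2, with predictor and residual SD both 1 (assumed). A test that treats the slope as common to all workers has inflation of about 1 + (m − 1) × 0.2²:
- m = 26: 1 + 25 × 0.04 = 2.00, error 17%
- m = 130: 1 + 129 × 0.04 = 6.16, error 43%

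Simulation with 30 workers gave about 16% and 41-44%. Estimating a slope for each worker and testing the slopes with a one-sample t-test gave about 5% in both cases. The remedy therefore needs a random slope.

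**The case against.** A reader might infer that the plan will produce p-values that are far too small. The documents do not support that. No sentence says that repeated rows will enter a correlation as if they were independent people. The sentence in section 2.6 describes export options of the wristband database; it does not define the analysis unit and does not cover the questionnaires. Section 2.7 also leaves the processing strategy to be chosen after a descriptive stage. This part of the objection stands.

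A reader might also infer that the plan fails its own objective by ignoring within-worker association. That too goes beyond the text. No objective asks about stressful weeks as such. The fourth can be read as one pattern per worker set against that worker's stress and quality-of-life level, and for that the listed tests are valid. Quality of life is measured only two or three times, so a weekly quality-of-life analysis is not possible. The Wilcoxon test does use the repeated scale rounds, although for change and not for association.

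The size also depends on assumed values: at ICC 0.05-0.1 with weekly data the pooled error is only 6-8%. And this is a pilot, with feasibility among its main aims.

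What does not stand is the reply that an unseen analysis plan settles the matter. The article is not silent. It names the tests for every association, at 5%, for a design it calls longitudinal, and limits none of them to one-value-per-worker summaries.

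**Conclusion.** The point holds as a conditional one and should be fixed. Section 2.7 commits all associations to tests that assume independent observations, while key variables are repeated daily, weekly or by the minute and nothing fixes the unit of analysis.

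If rows are pooled, the nominal 5% Pearson test rises to about 6-47% with 26 weekly records and about 9-73% with 130 daily records, over ICC 0.05-0.5. These figures rest on assumed ICCs, equal in both variables, and on exchangeable correlation within workers. If the data are accumulated to one value per worker, the error stays near 5%, but only differences between workers are tested. The article does not say which route will be taken.

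**What to change.** In section 2.7:

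1. State the unit of analysis for each association: worker, week or day.
2. Keep Pearson/Spearman, t-test/ANOVA (and their rank versions) and chi-square for one-value-per-worker summaries only.
3. For associations among daily, weekly and wristband variables, use mixed models with worker as cluster, ordinal where the 0-5 items need it. Split each time-varying predictor into the worker's mean and the deviation from it. Include a random intercept, a random slope for the within-worker term, serially correlated residuals and small-sample degrees of freedom. GEE with a small-sample correction is an alternative.
4. Name a fallback in case of non-convergence: estimate a within-worker slope for each person and test the slopes with a one-sample t-test.

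The data and software can stay as they are; SPSS has mixed-model procedures. The cost is revised wording, more analyst time and possible convergence problems in a small pilot, which the fallback addresses.

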## 3. Discussion

This pilot study may allow us to design a broader study with more participants in future. Stress is increasingly present in our society, and despite being historically understood as an expected effect derived from the mere activity of working, in recent years it has started to be considered as detrimental, but not unavoidable [69,70]. This kind of study could help with the control and detection of stress, influencing positively its reduction and improving the quality of life of workers [37]. In particular, if this study is successful, it would allow the evaluation of occupational stress by using cheap devices and easy-to-understand questionnaires that can be used by any person without any specific training. It would be possible to establish the influence that working stress has on the daily routines and occupational balance of workers.

In addition to the worldwide increase in stress, the emergence of coronavirus disease 2019 (COVID-19) has meant a significant worsening of the mental health of a large part of the population. Stress, along with anxiety and depression, have spread or become more severe during the pandemic in the general population [71]. Job instability due to unforeseeable lockdowns and restrictive measures leads to increased stress in the population, which along with precarious jobs, generates long-term uncertainty that can further increase general stress levels [72,73].

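### The article aims at causal, directional conclusions about work stress, but section 2.7 names only undirected tests, so an effect of stress cannot be told from the reverse

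*Protocol article*

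**What the plan says.** **Aims and intended conclusions.** Section 2.1 describes observation without intervention, "with the aim of establishing causal associations between variables". The main objective is to "assess the work stress level and its influence on the quality of life of workers at a research center". A specific objective concerns the impact of occupational stress on "daily life through the information from wristbands and questionnaires". Section 2.5 states: "The primary outcome will be to determine the influence of stress and anxiety on the worker". The Discussion says of a successful study: "It would be possible to establish the influence that working stress has on the daily routines and occupational balance of workers". The Conclusions likewise expect the data to show how stress influences quality of life.

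**Undirected wording.** The fourth specific objective is weaker: "To study the association between the identified patterns of occupational functioning, activity, and sleep, and the level of occupational stress and quality of life".

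**Analysis.** Section 2.7 says: "The association of numerical variables will be analyzed with the Pearson or" Spearman coefficient. Categorical pairs get a Chi-square or likelihood ratio test. Mixed pairs get a t-test or ANOVA, or their rank-based counterparts. A Wilcoxon test compares the initial, intermediate and final evaluations.

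**Data.** Wristbands record sleep, steps and heart rate for six months. Exhaustion, motivation and frustration are rated daily. Stress sources, sleep, activity and occupational balance are rated weekly. Section 2.6 places the four scales at the beginning and end; Table 1 and section 2.7 add a middle evaluation.

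**The concern.** The question has a direction: stress is to act on quality of life and daily routine. The named tests have none. A correlation of stress with sleep is the same number as a correlation of sleep with stress. The Wilcoxon test is the only one that uses time, and it asks whether a single measure changed, not whether earlier stress goes with a later outcome.

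Reverse effects are plausible here. A bad night can raise the next day's rating of work exhaustion, and poor health-related quality of life can raise perceived stress. A significant correlation would be equally compatible with these, yet the aims and Discussion invite the reader to take it as an effect of stress. The main objective and the primary outcome are both exposed. The time order that would help is in the data, but no named analysis uses it.

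**Working it through.** The article gives no sample size, effect size or power, so there is no figure to reproduce.

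**1. Symmetry (no assumptions about the trial).** In one artificial data set of 40 pairs, Pearson r = -0.556 (p = 0.00019) and Spearman rho = -0.508, whichever variable is named first. In a 2×2 table, Chi-square = 3.683 before and after transposing. The t-test and ANOVA family is not strictly symmetric, but it also carries no direction in time.

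**2. Purely reverse causation (all inputs assumed).** Take n = 30 workers and 180 days (about six months). Nightly sleep is a stable worker level with SD s plus a first-order autoregression (0.3, innovation SD 1). Stress on a day is -0.35 × the previous night's sleep, plus a worker effect (SD 0.5) and daily noise (SD 0.9). Stress has no effect on later sleep. Each worker is summarised by a mean; this is also an assumption, as 2.7 does not say how daily records enter the correlation.

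- Variance of mean sleep: Vs = s² + [1/(1 - 0.3)²]/180 = s² + 0.0113
- Variance of mean stress: Vy = 0.35² × Vs + 0.25 + 0.81/180
- Correlation: r = -0.35 × Vs / √(Vs × Vy)
- Chance of p < 0.05 (two-sided, Fisher z): about Φ(|atanh r| × √27 - 1.96)

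| s | Vs | Vy | r | atanh r × √27 | Chance significant |
|---|---|---|---|---|---|
| 0.7 | 0.501 | 0.316 | -0.441 | -2.46 | 69% |
| 0.3 | 0.101 | 0.267 | -0.216 | -1.14 | 21% |

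Separate simulations of this set-up gave 67% to 73% for s = 0.7 and 20% to 22% for s = 0.3. With no stable sleep differences between workers the rate falls to 6% to 8%, close to the nominal 5%. With s = 0.7 and n = 15, 20, 50 and 80, it was 40%, 51%, 91% and 98%.

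On the same data, a within-worker regression of the following night's sleep on the day's stress, given the previous night's sleep, was significant in about 4% to 6% of studies. That comparison is not like for like: one test is between workers, the other within workers, and the data were generated to suit the second.

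**3. Both directions side by side.** In a second simulation (26 weekly waves, autoregression 0.5, a stable person effect, N = 40, lagged effect 0.1), the correlation of person means was:

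- stress drives sleep: mean r = -0.483, significant in 89.5% of studies;
- sleep drives stress: mean r = -0.488, significant in 91.8%.

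With a lagged effect of 0.2, within-person cross-lagged coefficients separate the two cases: -0.206 (stress to sleep) and 0.016 (sleep to stress) when stress drives sleep; 0.015 and -0.204 when sleep drives stress.

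**4. Limits of lagged models.** With no effect of stress at all (assumed inputs, n = 30), a regression of final EQ 5D-5L on initial PSS-10 given initial EQ 5D-5L was significant in 29% to 58% of studies when both scales shared a stable trait. When stable quality of life drove stress and EQ reliability was 0.6 to 0.8, the figure was 14% to 30%. A daily lagged model was significant in 91% to 100% when autocorrelated workload affected both stress and sleep.

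**The case against.** The strongest defence is that section 2.7 speaks of association and possible relationships, one specific objective does the same, and the study is a pilot on feasibility and sample size. The article condenses a fuller plan that could contain lagged models, and 2.7 itself leaves the processing strategy open. Rewording alone would remove the contradiction.

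Much of this stands. The absence of a lagged model would not be a fault by itself. The fault is that the same article states a causal aim, names the tests meant to serve it and announces directional conclusions. Pilot status does not change that, since the Discussion and Conclusions still promise the influence of stress.

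Two stronger readings are tempting. A reader might infer that the study will report an effect of sleep on stress as an effect of stress. The documents do not say so: that is a risk opened by the wording, and the restriction to measurements from the same period is likewise inferred from the schedule and the absence of any lag. A reader might also infer that lagged results would earn the word influence. Step 4 of the working shows that they would not: lagging deals with order, not with common causes or measurement error.

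**Conclusion.** The mismatch holds and is in the text: causal and directional aims are paired with tests that carry no direction and do not link stress to later outcomes. What follows is that direction is not identified, not that the conclusion will be wrong.

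The symmetry needs no assumptions. The size does. Under purely reverse causation with 30 workers, the correlation of worker means would be significant in about 20% to 73% of studies for stable sleep differences of SD 0.3 to 0.7. These figures are illustrative, because the sample size, the effect and the use of worker means are all assumed. The point merits correction before analysis because it touches the main objective and primary outcome.

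**What to change.** 1. **Aims and conclusions.** Reword sections 2.1 and 2.5, the objectives, the Discussion and the Conclusions to association. State in 2.7 that the correlations and group comparisons give no information on direction.
2. **Lagged models in both directions, from data already collected.** Within workers, relate the day's exhaustion and frustration items to the following night's sleep and the next day's steps, given prior values. Beside these, relate a night's sleep to the next day's items, also given prior values. For the scales, fit baseline-adjusted models both ways (for example later EQ 5D-5L on earlier PSS-10, and the mirror). Include the intermediate wave if it is confirmed once section 2.6 is reconciled with section 2.7 and Table 1.
3. **Interpretation.** Describe lagged results as evidence on temporal order. Adjust for confounders already on the record sheet, such as working hours, overtime, non-work stress factors and medication, and say that unmeasured workload and imperfect scale reliability may remain.

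No new data or visits are needed. The cost is a change of wording, modest extra analysis and a less favourable headline claim.

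### The sparse-table rule is triggered by observed percentages instead of expected counts, and its likelihood-ratio fallback is no safer than chi-square and often more liberal

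*Protocol article*

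**What the plan says.** Section 2.7 gives a complete rule for two categorical variables, with a default test, a trigger and a fallback: "the Chi-square test will be applied, or the likelihood ratio in the case that the frequencies observed are less than 5" (a per cent sign follows the 5). No exact test is named. On the error rate it states: "The significance level for hypothesis testing is set at 5" per cent. The software is fixed as well: "The statistical treatment of the data will be performed with the statistical package IBM SPSS Statistic version 22".

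Three other places show where the rule would apply. Section 2.1 says "This project will be a pilot study". Section 2.2 describes a single research centre and adds "Sample selection will be performed through intentional sampling based on inclusion and exclusion criteria". Section 2.6 collects, among other items, "age, gender, marital status, residential environment, cohabitation unit, educational level, profession, socio-economic level". Section 2.4 gives no number of participants. It expects the pilot to supply the information "which will allow us to carry out the calculation of the sample size".

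**The concern.** A rule of this kind should identify tables in which the chi-square reference distribution is a poor approximation, and then move to a test that does not need it. This rule does neither reliably.

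- **Trigger.** The quality of the approximation is governed by the counts expected under independence. An observed cell can be small because the association is strong, with every expected count ample. It can also be an unremarkable share of a very small sample in which every expected count is low. Stating the threshold as a percentage makes it drift further from the expected count as N changes.
- **Fallback.** The likelihood-ratio statistic is referred to the same chi-square distribution and needs the same large-sample conditions.

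A safeguard that raises the false-positive rate would defeat its purpose. Section 2.7 plans significance tests to look for relationships between variables, and a small single-centre sample with several multi-category characteristics could produce sparse tables.

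**Working it through.** **Inputs.** From section 2.7: level 0.05, chi-square default, observed-percentage trigger, likelihood-ratio fallback. Assumed, because the article gives neither: sample size and category proportions. The article states no error rate for the rule, so there is no figure to reproduce.

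**Formulas.** Expected count E = (row total × column total) / N. Pearson X² = Σ(O − E)²/E. Likelihood ratio G² = 2 Σ O ln(O/E). Both are compared with the chi-square distribution on (r − 1)(c − 1) degrees of freedom. The trigger is read as any cell below 5% of N.

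**Step 1: does the trigger find sparse tables?**

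| Table | Smallest observed cell | Smallest expected count | Rule switches? |
|---|---|---|---|
| [[2,8],[2,8]], N = 20 | 2/20 = 10% | 10 × 4/20 = 2 | No |
| [[8,192],[8,192]], N = 400 | 8/400 = 2% | 200 × 16/400 = 8 | Yes |
| [[1,19],[19,1]], N = 40 | 1/40 = 2.5% | 20 × 20/40 = 10 | Yes |

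The one sparse table is left alone, and the two adequate ones are switched.

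**Step 2: what does the fallback do in one table?** Take 0/20 against 3/20. The expected counts are 1.5 and 18.5 in each group.

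- X² = 40 × (0 × 17 − 20 × 3)² / (20 × 20 × 3 × 37) = 144,000/44,400 = 3.24, p = 0.072.
- G² = 2 × [20 ln(20/18.5) + 3 ln(3/1.5) + 17 ln(17/18.5)] = 4.40, p = 0.036.
- Fisher, two-sided: 2 × C(20,3)/C(40,3) = 2 × 1,140/9,880 = 0.231.

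The empty cell fires the rule, so the result is reported as significant when neither chi-square nor Fisher finds it so.

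**Step 3: true size in 2x2 tables.** This is exact: the probabilities of all outcomes of two binomials with a common p, summed over the outcomes that reject.

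| Groups | p | Chi-square | Plan's rule | Fisher |
|---|---|---|---|---|
| 10 + 10 | 0.10 | 0.9% | 4.9% | 0.1% |
| 10 + 10 | 0.20 | 3.0% | 7.3% | 0.8% |
| 15 + 15 | 0.10 | 2.5% | 7.8% | 0.6% |
| 15 + 15 | 0.20 | 5.0% | 6.7% | 1.7% |
| 20 + 20 | 0.10 | 3.9% | 8.5% | 1.2% |
| 20 + 20 | 0.20 | 5.0% | 5.5% | 2.3% |

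Outside this range the rule's size varies. It is 9.1% at 40 + 40, p = 0.05 (chi-square 4.3%), and only 3.7% at 10 + 30, p = 0.10 (chi-square 2.8%). Over 35 settings (group sizes 10 to 40, p from 0.05 to 0.5), the size of the likelihood-ratio test was never below that of chi-square.

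**Step 4: larger tables.** These sizes were simulated under independence with 20,000 to 40,000 tables each.

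- In moderately sparse 2x4, 3x3 and 3x4 tables with N = 20 to 60, chi-square gives 3.5 to 4.9% and the plan's rule 6.2 to 10.5%. For example, 3x3 with equal margins and N = 30 gives about 4.7% for chi-square and 8.5% for the likelihood ratio.
- In strongly skewed tables the order reverses. 3x3 with margins 0.8/0.1/0.1 and N = 20 gives about 11% for chi-square and 3% for the likelihood ratio. 4x4 with margins 0.7/0.1/0.1/0.1 and N = 30 gives about 9% and 2%.

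**The case against.** **The likelihood-ratio test is not always the more liberal one.** A reader might infer from the 2x2 results that the fallback generally inflates false positives. The article does not support that. It gives no category proportions, and characteristics such as marital status or profession could well be unevenly distributed. In the skewed tables of Step 4 the likelihood ratio is the conservative test and chi-square the liberal one. This objection stands and limits the point. It does not rescue the rule, because its trigger cannot tell the two situations apart.

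**The excess depends on the event probability.** With 10 to 20 per group and p between 0.3 and 0.5, the rule's size is 4.3 to 5.6%, close to nominal. This also stands.

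**The trigger alone shows little harm in 2x2 tables.** Where it wrongly leaves a sparse 2x2 table with chi-square, chi-square was at or below about 5% in the settings of Step 3. This is fair: in 2x2 tables the inflation comes mainly from the fallback.

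**The per cent sign may be a slip for a count of 5.** That is possible but cannot be shown. Under that reading the trigger still uses observed cells. The sizes at p = 0.10 with 15 + 15 and 20 + 20 are unchanged, and at 10 + 10, p = 0.20 the size rises from 7.3% to 8.7%.

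**The tests are peripheral.** Most outcomes are numerical (steps, sleep, heart rate, scale scores) and go to other tests, and the study is a pilot. This stands and lowers the impact. A reader might also infer that most of the categorical tests will be governed by this rule. With no sample size and no list of planned cross-tabulations, that cannot be established.

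**It could be left to a fuller analysis plan.** That would excuse a missing rule. Here a specific rule is stated, and it is wrong as stated.

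**Conclusion.** The point holds in a limited form. The trigger uses the wrong quantity, which needs no assumption to show. The fallback shares the weakness it is meant to avoid: it is no safer than chi-square in sparse tables and is often more liberal.

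The size of the effect rests on assumed sample sizes and proportions. It is at most 3.5 percentage points above nominal in the balanced 2x2 range examined (8.5 − 5.0), and up to about 5.5 points in moderately sparse larger tables (10.5 − 5.0). In strongly skewed larger tables the fallback errs on the conservative side. A general claim that the rule raises the false-positive rate in this study would go beyond the article.

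The sentence should be corrected. The impact is moderate, since no primary hypothesis depends on these tests.

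**What to change.** Replace the sentence in section 2.7 with a rule along these lines: use the chi-square test when expected counts are adequate (for example, all at least 5 in a 2x2 table, or no more than 20% of cells below 5 in a larger one). Otherwise use Fisher's exact test for 2x2 tables, and the Fisher-Freeman-Halton test or Monte Carlo exact p-values for larger ones. Delete the likelihood-ratio option and the 5% criterion. The cut-offs are conventions. What matters is that they refer to expected counts and are fixed in advance.

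For 2x2 tables with 10 to 40 per group and p from 0.05 to 0.5, this rule has size between 0.01% and 5.7%. It exceeds 5% only where chi-square itself is used.

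The edit is one sentence. The statistical cost is conservatism, which is marked in small 2x2 tables (Fisher's size is 0.1 to 2.3% in the range examined) and brings some loss of power. The team should also confirm that its SPSS installation can produce the exact and Monte Carlo results for larger tables.
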